**Abstract**

**Introduction:** PrEP (pre-exposure prophylaxis) is medicine people at risk for HIV take to prevent them from getting HIV. Senegal is in the process of rolling out PrEP gradually nationally. Female sex workers are one of the target groups for PrEP due to their high risk of contracting HIV. However, there is also a policy concern that taking PrEP might reduce their incentives for using a condom, especially when unprotected sex has higher renumeration. This may have public health consequences as condom use also curbs the transmission of other sexually-transmitted infections (STIs). Therefore, this study aims to study whether the drop in condom use is large enough to be of concern, and if possible, among which groups this drop is concentrated in.

**Methods and Analysis**: This study is a randomised controlled trial with two parallel groups. 1 Female sex workers aged 18 and over who took part in the July 2020 wave of a panel survey held in Dakar, Senegal who are still working in sex work at the point of that survey

**Ethics and Dissemination:** This trial has been prospectively registered with the ISRCTN Registry. We obtained ethical approval from Senegal National Ethics Committee and the UCL ethics committee before data collection. The findings of the trial will be published in peer-reviewed journals irrespective of the final results.

**Trial registration**:

ISRCTN16445862. Registered on 11 March 2021.

**Funding:**

This project is funded by a MRC grant awarded to [name] [name] MR/T00262X/1 and a grant from Erasmus university

**Keywords**

Randomised controlled trial; PrEP; vulnerable women; STIs/HIV

**Introduction**

**Background and rationale {6a}**

When taken as prescribed, pre-exposure prophylaxis (PrEP) is highly effective in preventing HIV infection [1-2]. However, there is some concern that this protection may encourage risky sexual behaviour—*risk compensation—*that partially offsets the preventive effect [2-7]. For example, taking PrEP may reduce condom use or increase sexual activity with multiple partners. Such behaviours would increase the prevalence of other sexually-transmitted infections (STIs) that PrEP does not protect against.

Most research on behavioural responses to PrEP have focused on men who have sex with men (MSM). Evidence of risk compensation in this population is mixed [2, 8-10]. It is more evident in more recent studies [8-10]. This is consistent with an increasing behavioural response as awareness of PrEP’s effectiveness becomes more widespread [8-9].

Risk compensation could potentially be more prevalent among sex workers taking PrEP as they have an economic incentive to adopt riskier sexual behaviours. For example, they can charge a higher price for condomless sex [2, 11]. However, there is a lack of robust evidence on the phenomenon in this population. Observational studies have shown mixed evidence [7, 11, 13-14] that is difficult to interpret because sex workers who take PrEP have been observed to have riskier sexual behaviours and be at higher risk of STIs at baseline [16]. Qualitative research suggests that risk compensation may grow as sex workers become more convinced of the effectiveness of PrEP [12]. On the other hand, PrEP provision may bring hard-to-reach populations such as sex workers into closer contact with the health system, improving opportunities for routine STI testing and sexual health counselling [3].

In 2021/2022, Senegal rolled out PrEP to target high-risk populations, including female sex workers. Before the rollout, PrEP had been temporarily offered to only a limited cohort of female sex workersIn 2015, HIV/AIDS prevalence among female sex workers (6.6 percent) was nine times higher than the overall prevalence rate [18]. In Senegal, sex work is legal upon registration. Registered sex workers are required to visit a public health centre every month for health checks. Due to the strong stigma attached to sex work, many sex workers choose to remain unregistered.

This study aimed to use the rollout of PrEP to female sex workers in Senegal to obtain the first randomized experiment evidence for this high-risk population on risk compensation in response to PrEP.

**Objectives {7}**

Pre-exposure prophylaxis (PrEP) reduces the use of condoms among female sex workers.
2. PrEP reduces the perceived necessity of the use of condoms among female sex workers.

**Trial design {8}**

This study is a randomised controlled trial. We identified 500 respondents who were potentially eligible for PrEP and randomly assigned them into treatment and control groups (3:2). The randomization was stratified by (a) reported prior experience with PrEP in the 2015/16 PrEP pilot study, and (b) self-reported sexual risk-taking reported in the 2020 survey.

**Methods: Participants, interventions and outcomes**

**Study setting {9}**

PrEP initiation and follow-up for female sex workers (FSWs) was implemented by the Ministry of Health (MoH) and Social Action Senegal through public health facilities responsible for delivering prevention and treatment services mainly to registered sex workers and by the Alliance Nationale Contre le SIDA (ANCS) through community sites and mobile clinics that mainly target unregistered sex workers.

**Eligibility criteria {10}**

Our sampling frame came from a survey of 604 FSWs conducted between June and August 2020 in Dakar, Senegal. The survey was the third wave of a cohort study, initiated in 2015 and followed-up in 2017, that interviewed FSWs who were at least 18 years old. In each survey wave, the sample was replenished with new participants who were recruited via snowball sampling by midwives at public health centres (registered sex workers) and sex worker facilitators (unregistered sex workers).

We identified participants who were potentially eligible for PrEP by excluding those who were not active in sex work in 2020 and those who were recorded as having a medical record of being HIV positive in any of the previous surveys. We identified 500 respondents who were potentially eligible for PrEP and randomly assigned them into treatment and control groups (3:2). The randomization was stratified by (a) reported prior experience with PrEP in the 2015/16 PrEP pilot study, and (b) self-reported sexual risk-taking reported in the 2020 survey.

**Who will take informed consent? {26a}**

Trained enumerators take informed consent by reading and explaining the information sheets (containing information on the study, objectives of the research, risks and benefits and explaining that participation is voluntary) to potential participants. Participants then have the opportunity to have an informed discussion with the enumerators regarding the study. Participants 21 years old and over are considered majors. Majors can offer their own consent to participate in the study. Adult representatives offering consent and all participants (minor and major) will receive a hard copy of the consent. An electronic copy, for researchers, of all consent forms (adult representative, minor, major) is stored electronically using an ODK-based survey.

**Additional consent provisions for collection and use of participant data and biological specimens {26b}**

Participants are informed during the informed consenting process that they will undergo biological. From October 2021 to January 2022, midwives and FSW peer facilitators working for MoH and ANCS approached potential participants in the treatment arm, informed of the availability of PrEP and asked if they were interested in receiving the medication. Interested participants continued to PrEP screening to establish whether each was still a FSW and satisfied medical criteria for PrEP eligibility: (a) good liver function assessed by creatinine level, (b) HIV negative, and (c) not pregnant. Those in the treatment group who eventually did not take up PrEP because they either were found to be ineligible or refused PrEP were not excluded from a survey used to measure outcomes. After this survey, potential PrEP candidates in the control arm were offered PrEP if they reported still being in sex work and they met the medical criteria. It is explained to participants that the reason we collect their data and biological specimens is to meet the research objective. Consent for biological specimens required for infection testing, using vaginal swabs and blood tests, is obtained during the consenting process.

**Interventions**

**The explanation for the choice of comparators {6b}**

The trial will compare participants who receive PrEP with participants who receive nothing.

**Intervention description {11a}**

From October 2021 to January 2022, midwives and FSW peer facilitators working for MoH and ANCS approached potential participants in the treatment arm, informed of the availability of PrEP and asked if they were interested in receiving the medication. Interested participants continued to PrEP screening to establish whether each was still a FSW and satisfied medical criteria for PrEP eligibility: (a) good liver function assessed by creatinine level, (b) HIV negative, and (c) not pregnant. Those in the treatment group who eventually did not take up PrEP because they either were found to be ineligible or refused PrEP were not excluded from a survey used to measure outcomes. After this survey, potential PrEP candidates in the control arm were offered PrEP if they reported still being in sex work and they met the medical criteria. At the end of the trial, PrEP was rolled out to the control group.

**Recruitment start date**

10/2021

**Recruitment end date**

01/2022

**Criteria for discontinuing or modifying allocated interventions {11b}**

All adverse events will be treated on a case-by-case basis. In the event of an unanticipated adverse event that may cause direct harm or threat to the participants or others that are related to study implementation. An unanticipated event report will be submitted promptly to the Senegal National Ethics Committee and the UCL ethics committee per protocol.

**Strategies to improve adherence to interventions {11c}**

The main strategies employed to encourage participant adherence to the intervention is to ensure that participants have the best possible experience whilst receiving PrEP. The community based organisation CBOs and specifically peer leaders and mobilisers support the adherence of participants to the intervention by keeping in regular contact with the participants throughout the lifetime of the project. Regular contact allows participants with concerns regarding the project or the intervention specifically the opportunity to speak up. Any problems are communicated to the research team and resolved. All resolutions are discussed with the participants. Peer leaders and mobilisers use their strong relationships with the participants and their status in this vulnerable population to engage participants and encourage adherence to the intervention.

**Relevant concomitant care permitted or prohibited during the trial {11d}**

There are no restrictions on concomitant care.

**Provisions for post-trial care {30}**

Any participants who suffer harm, e.g., psychological distress, as a consequence of the trial will be supported by the relevant CBO's psychological support services. Those in the control group, that remain in the study until the end of the project, will receive the same intervention at the end of the trial

**Outcomes {12}**

**Overview**

In April-May 2022, the midwives and FSW peer facilitators attempted to reach and interview in a survey all 500 candidates who had been randomized to the treatment or control arms. The survey covered PrEP usage, preventive health behaviours and details of the sex work undertaken. We had limited access to health system information on which participants eventually received PrEP medication. We relied predominantly on the self-reported survey data on PrEP usage. For those who reported using PrEP, this was cross-checked with midwives for registered sex workers and FSW peer facilitators for unregistered sex workers.

### Primary outcome measures

Measured with a survey expected to be held 3 months after the roll-out of PrEP:
1. Condom use with each of the last two clients and the last five clients measured via a combination of these methods:
1.1. Via direct questioning
1.2. Via list experiment
1.3. Via a newly-designed instrument aimed at eliciting individual condom use without compromising respondent confidentiality
2. Subjective perceptions of the necessity of condom use measured using a Likert-like scale

### Secondary outcome measures

Measured with a survey expected to be held 3 months after the roll-out of PrEP:
1. Number of occasional and regular clients seen in a fixed time frame, e.g. 7 days
2. Perceived HIV risk of clients
3. Price of each of the last two clients
4. Type of sex acts with last two clients/stayed overnight with last two clients
5. Earnings from sex work in a fixed time frame, e.g. 30 days
6. Household expenditure in a fixed time frame, e.g. 30 days
7. Food insecurity
8. Self-reported STI symptoms with last two clients
9. Mental health measured using the PHQ-9 questionnaire

**Participant timeline {13}**

[figure not shown]

Figure 1: Schedule of enrolment, interventions, and assessments

**Sample size {14}**

Our sampling frame came from a survey of 604 FSWs conducted between June and August 2020 in Dakar, Senegal. The survey was the third wave of a cohort study, initiated in 2015 and followed-up in 2017, that interviewed FSWs who were at least 18 years old. In each survey wave, the sample was replenished with new participants who were recruited via snowball sampling by midwives at public health centres (registered sex workers) and sex worker facilitators (unregistered sex workers).

We identified participants who were potentially eligible for PrEP (Figure 1) by excluding those who were not active in sex work in 2020 and those who were recorded as having a medical record of being HIV positive in any of the previous surveys. We identified 500 respondents who were potentially eligible for PrEP and randomly assigned them into treatment and control groups (3:2).

**Recruitment {15}**

In April-May 2022, the midwives and FSW peer facilitators attempted to reach and interview in a survey all 500 candidates who had been randomized to the treatment or control arms. The survey covered PrEP usage, preventive health behaviours and details of the sex work undertaken. We had limited access to health system information on which participants eventually received PrEP medication. We relied predominantly on the self-reported survey data on PrEP usage. For those who reported using PrEP, this was cross-checked with midwives for registered sex workers and FSW peer facilitators for unregistered sex workers.

**Assignment of interventions: allocation**

We used computer based randomisation and allocated participants in the group. We then sent lists of participants to recruit to the implementing CBOs and health facilities to recruit participants. Only participants on the list were eligible to PrEP.

**Assignment of interventions: Blinding**

**Who will be blinded {17a}**

Participant allocation to the treatment arm is known by the participants, the enumerators and supervisors. However, data analysts will be blinded during the data analysis period.

**Data collection and management**

**Plans for assessment and collection of outcomes {18a}**

Outcomes are measured via the biobehavioural and socioeconomic survey. The survey questionnaire will include sociodemographic questions, income, health status, demand for healthcare, economic shocks, STI prevention, risky sexual behaviours, violence, personality traits and preferences.

**Plans to promote participant retention and complete follow-up {18b}**

**Participant retention**

Participants are not incentivised or coerced to participate in the study. During the informed consent process, the benefits of the study are outlined in detail to encourage participant retention. The primary benefit highlighted is the possibility that this project will contribute to the proposal of public policy intervention to improve the quality of life of young women who engage in transactional and commercial sex.

In addition, all participants receive compensation for their time and travel costs. Participants are compensated 2000 FCFA for their time and travel when responding to on-site questionnaires. This compensation will act to reduce any barriers to participant participation (e.g., transport fees).

To retain participants in the control group, the project offers the same intervention to all eligible control group participants at the end of the data collection period.

**Participant withdrawal**

Participation is voluntary and participants can withdraw at any time, without giving reasons, by notifying a project staff member. Participant information already collected will be suppressed from the dataset. Withdrawal of participants on the treatment arm of the study will not impact any services or medical treatment they receive or any relationships they have with those treating them outside of the project.

**Data management {19}**

Socioeconomic questionnaires will be administered by enumerators in the field. All potential participants will be screened before recruitment onto the study to ensure they have not already participated. Participant responses are entered directly into an ODK-based questionnaire using Android tablets and uploaded to the ODK secure server in the UK when a 3G/WIFI connection is available (immediately, or at the end of each day). On survey completion, the data will be transferred to the UCL Secure Server, a fully encrypted (SSL) server with a direct data link to the android device. The ODK-based questionnaire is programmed with a logic that minimises missing data (e.g., enumerators will not be able to skip questions) and data quality (e.g., range checks will be conducted regularly). Any issues regarding data quality will be reported to the Principal investigator (PI) and directly to the enumerators and the team in the field.

All data will be stored in accordance with University College London's data storage policies.

After completion of the project, data will be made openly available through the UCL data repository, subject to the ability to remove personally identifiable information. Data will be deposited with UCL research data repository (<https://www.ucl.ac.uk/library/research-support/research-data-management/ucl-research-data-repository>), where it will be given a Digital Object Identifier (DOI). The DOI will be cited in project reports and journal publications through a Data Access Statement or citation list. Metadata will also be made available to 3rd party research catalogues, such as https://datamed.org/.

Anonymised data will be made openly available using a permissive licence, such as Creative Commons Attribution (CC-BY). If complete anonymity cannot be provided, it will be made available through a controlled access system. If data must be made available via controlled access, interested parties will be asked to provide information on their research (purpose, institutional affiliation, ethics approval) and sign a data sharing agreement indicating they will comply with the consent form and will not attempt to re-identify individuals. Access requests will be evaluated by the project team in the first instance. In cases where an access request is denied and the requester wishes to appeal, the request will be escalated to the UCL Research Governance Committee for consideration.

**Confidentiality {27}**

The following measures have been put in place to ensure data confidentiality and to respect the privacy of participants:

1. Implementation of and compliance with the code of ethics

All study staff, inclusive of hired and trained experienced local enumerators and interviewers, must sign a commitment to comply with the code of ethics. Research partners with access to data have signed a sub-contract with a clause which ensures that all data collected must remain confidential.

1. Participation is confidential

Socioeconomic and biobehavioural data collection will be conducted in a private location at the CBOs or health facility. Participants must not share a telephone to be enrolled in the SMS survey..

1. Secure storage of data

During the trial, all paper-based records will be kept securely in a locked cabinet, in a locked office, and securely transferred to the Ministry of Health office where they will be transferred to a centralized, 128-bit encrypted and password-protected database. All electronic data will be stored on the UCL Secure Server.

1. Aggregation and anonymisation of data

Individual responses will be deidentified and aggregated for analysis and reporting. All published findings, including any quotes used, will not allow for individuals to be identified. All results will be presented in aggregate form.

**Plans for collection, laboratory evaluation and storage of biological specimens for genetic or molecular analysis in this trial/future use {33}**

N/A

**Statistical methods**

**Statistical methods for primary and secondary outcomes {20a}**

All statistical analyses will be conducted using STATA. Descriptive statistics will first be used to summarise participant characteristics between the study groups. To investigate the effect of health insurance on primary and secondary outcomes, the analysis will use an intention-to-treat (ITT) approach where participants will be analysed in their allocated randomised study group. If there are non-compliers, we will also estimate the local average treatment effect (LATE). Outcomes for the treatment versus the control group will then be compared accounting for any baseline or attrition differences using ordinary least squared.

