**Methods for additional analyses (e.g., subgroup analyses) {20b}**

Further analysis will investigate if the effect of PrEP varies depending on the factors used for stratification.

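### The primary OLS adjusts for whatever baseline or attrition differences appear, a rule that would practically never bring in the factors used to stratify randomisation

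*Protocol*

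**What the plan says.** The Protocol describes a stratified design in Trial design {8}, and again under Eligibility criteria {10}: "The randomization was stratified by (a) reported prior experience with PrEP in the 2015/16 PrEP pilot study, and (b) self-reported sexual risk-taking" as reported in the 2020 survey. Allocation is 3:2 among 500 women.

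The analysis is set out in Statistical methods for primary and secondary outcomes {20a}. Descriptive statistics come first. The population is by assignment: "the analysis will use an intention-to-treat (ITT) approach where participants will be analysed in their allocated randomised study group". A LATE is added if there are non-compliers. The arms are then "compared accounting for any baseline or attrition differences using ordinary least squared". No covariate is listed and nothing says what counts as a difference.

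The stratification factors appear in the analysis sections only once, in {20b}, for effect heterogeneity: "Further analysis will investigate if the effect of PrEP varies depending on the factors used for stratification".

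**The concern.** The sentence in {20a} is a rule, even if a loose one. The arms are described, and the comparison then takes account of the differences found. Attrition differences cannot be known until the April-May 2022 outcome survey is in, so on a plain reading the covariate set is settled only once outcome data exist.

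Two things follow. First, the rule works against the design. Stratification makes the arms alike on prior PrEP experience and 2020 risk-taking, so those factors will show no difference and give no reason to adjust. Yet the standard error is right only if the model accounts for them. Second, with no criterion and no candidate list, several defensible models could be fitted and one chosen after the results are visible.

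What is at stake is mainly precision. The trial asks whether a fall in condom use is large enough to worry about. An interval that is wider than it need be makes such a fall easier to miss.

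**Working it through.** The Protocol states no significance level, power, effect size, standard deviation or attrition rate, so there is no figure of its own to reproduce. The inputs taken from it are 500 women at 3:2 (500 × 3/5 = 300 and 500 × 2/5 = 200), the two stratification factors, and the adjustment sentence. All values of R² below are assumptions.

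**Step 1: effect of leaving out the strata.** Let the strata explain a share R² of outcome variance σ². Under stratified randomisation the difference in means has variance (1 − R²)σ²(1/300 + 1/200), because the between-stratum part is balanced out. OLS without the strata still estimates σ²(1/300 + 1/200). So:

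- width ratio = 1/√(1 − R²)
- actual coverage of a nominal 95% interval = 2Φ(1.96/√(1 − R²)) − 1

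| Strata R² (assumed) | Width ratio | Coverage | Type I error |
|---|---|---|---|
| 0 | 1.000 | 95.0% | 5.0% |
| 0.02 | 1.010 | 95.2% | 4.8% |
| 0.05 | 1.026 | 95.6% | 4.4% |
| 0.10 | 1.054 | 96.1% | 3.9% |
| 0.20 | 1.118 | 97.2% | 2.8% |
| 0.30 | 1.195 | 98.1% | 1.9% |

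The error runs in one direction only: too wide, never too narrow.

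**Step 2: would the stated rule pick up the strata?** This was simulated with 4,000 trials per setting, N = 500, 3:2 allocation within four strata (assumed shares 10%, 10%, 40%, 40%), no treatment effect, and one further baseline covariate that was not stratified on. The Protocol gives no criterion for a difference, so p < 0.05 was assumed. The fixed model holds the strata and the baseline covariate in every trial. Standard errors are in outcome SDs.

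| R² strata / baseline | Strata selected | Baseline selected | Rule: mean SE (true SD) | Rule: type I | Fixed: mean SE (true SD) | Fixed: type I |
|---|---|---|---|---|---|---|
| 0.05 / 0.10 | 0% | 5.2% | 0.091 (0.089) | 0.047 | 0.084 (0.085) | 0.054 |
| 0.10 / 0.10 | 0% | 5.2% | 0.091 (0.085) | 0.036 | 0.082 (0.081) | 0.050 |
| 0.10 / 0.20 | 0% | 5.0% | 0.091 (0.084) | 0.031 | 0.076 (0.076) | 0.050 |
| 0.20 / 0.10 | 0% | 4.8% | 0.091 (0.080) | 0.025 | 0.076 (0.076) | 0.048 |

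The Monte Carlo error on a 5% rate is √(0.05 × 0.95/4000) = 0.003, so the first row is compatible with 5% under both approaches and the other three show a conservative rule. The strata were never selected. In the third row the fixed model cuts the mean SE from 0.0908 to 0.0764, and 1 − 0.0764/0.0908 = 16%.

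**Step 3: what this means for detectable effects.** With 80% power and two-sided 5% (both assumed) and all 500 women surveyed, the minimum detectable difference is (1.960 + 0.842) × √[(1/300 + 1/200)(1 − R²)] outcome SDs, where R² is now the share explained by all covariates in the model. This gives 0.256 at R² = 0, 0.243 at 0.10, 0.229 at 0.20 and 0.214 at 0.30.

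**The case against.** The strongest reply is that the full covariate list, stratum indicators and type of standard error usually sit in a statistical analysis plan, which is not at hand, and that nothing in the Protocol forbids adjusting for the strata. The second half stands: silence is not exclusion. The first half answers only part of the point, because {20a} is not silent about how covariates arise. A later plan would have to replace that rule, not fill in its detail.

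Other objections also have weight:

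- **Size and direction.** No R² is documented, and the width error is small if the strata are weakly prognostic. Only omitted stratification factors make the nominal interval too wide. Leaving out an ordinary baseline covariate loses precision but leaves the interval valid. Because 2020 risk-taking is itself a stratification factor, gains from the strata and from baseline behaviour overlap.
- **The simulation tests a mechanical trigger.** It puts no figure on the bias that discretionary covariate choice could cause, so none is claimed here.
- **Blinding.** Section {17a} says "However, data analysts will be blinded during the data analysis period". That gives some protection. The 3:2 arm sizes could reveal the arms, but the Protocol does not say how masking is done or whether analysts hold PrEP-use data at that stage, so its strength cannot be judged.
- **Data held.** The documents establish 2020 sexual risk-taking and prior PrEP experience. They do not establish a 2020 condom-use value comparable with the outcome.
- **Timing.** The Protocol reports the outcome survey in the past tense, so a covariate set written now follows data collection. That favours a set dictated by the design.

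A reader might also infer inflated type I error, because the primary outcome is "Condom use with each of the last two clients and the last five clients" and OLS on client rows would treat one woman's clients as independent. With an assumed within-woman correlation of 0.5, the design effects 1 + (m − 1) × 0.5 are 1.5 for two clients and 3.0 for five, and type I error would be 11% and 26%. The documents do not support this reading: nothing says the rows are clients, and {20a} speaks of analysing participants.

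**Conclusion.** The point holds as one of precision and pre-specification. Section {20a} ties adjustment to observed differences, gives no criterion, and does not name the stratification factors, which such a rule would practically never select.

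Model-based intervals are then too wide by about 1%, 2.6%, 5.4% or 11.8% for an assumed strata R² of 0.02, 0.05, 0.10 or 0.20, and by nothing if R² is 0. These figures assume that the strata are left out and that conventional model-based standard errors are used. The estimate is also exposed to covariate choice after the data are seen, an exposure that cannot be sized from the documents.

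Two stronger conclusions are tempting and not supported. The Protocol does not exclude the strata or 2020 behaviour from the model. Nor does it set up an invalid primary analysis, since the width error is conservative. The change should be made, but the trial does not stand or fall on it.

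**What to change.** Replace the adjustment sentence in {20a} with wording such as:

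> The ITT effect is estimated by OLS of the outcome on assigned arm, randomisation-stratum indicators (prior PrEP experience, 2020 sexual risk-taking) and the 2020 value of the outcome where it was measured, with robust standard errors. This set is used whatever the observed balance, and the same covariates are used for the LATE.

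Three additions complete it:

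- Attrition differences are examined in a separate, specified sensitivity analysis and do not alter the main model.
- The list-experiment outcome uses the same covariates, together with a list-version term and its interaction with arm, because a single regression on arm does not fit that measure.
- If any outcome is analysed with clients as rows, standard errors are clustered by woman.

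The cost is a few lines of text and no new data collection: the stratum variables were needed to randomise. The change should be dated and made before any unblinded comparison, with a note that it follows the outcome survey. If such a comparison has already been run, the fixed model should be reported alongside it and the order stated.
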